**Outcomes**

The primary outcome is the proportion of DNT ≤ 60 min in the AIS treated with IVT, indicating a fast thrombolytic treatment from hospital arrival. The secondary outcomes include the key time intervals between assessment and thrombolytic treatment (median DNT, ONT), mRS score and death at discharge, complications after IVT [symptomatic intracranial hemorrhage (sICH)] and favorable functional outcomes (score of 0 to 1 on the mRS at 90 days), which indicate the efficiency and safety of PEITEM intervention. The DNT is defined as the time between hospital arrival and the initiation of IVT. The ONT is defined as the time between the symptom onset and the initiation of IVT. sICH is defined as intracranial hemorrhage at 24 hours associated with an increase of ≥4 points of NIHSS score from baseline, according to European Cooperative Acute Stroke Study (ECASS) II trial.^18^

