**Sample size**

A pre-randomization survey in the pre-intervention period at participating clusters was conducted. The proportion of AIS patients receiving IVT with DNT ≤ 60 minutes in China was 62%. Based on the outcomes reported by previous studies, a sample size estimation with a change from 55% to 70% of patients with DNT ≤ 60 minutes is clinically important.^10^ Therefore, a total of 1424 patients at 22 hospitals will be required to detect a 15% improvement in AIS patients with DNT ≤ 60 minutes, with 80% power, 5% significance level, and an intracluster correlation coefficient (ICC) of 0.05.

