**Statistical Analysis Plan**

We will use the intention-to-treat analysis to analyze all outcomes. The baseline characteristics of hospitals and patients will be analyzed between the PEITEM and control groups. We will summarize continuous variables as median with interquartile ranges and categorical variables as frequency and percentage, and analyze them by using Wilcoxon rank-sum test and Chi-square test separately. Modes will be used to impute missing values of categorical variables, and medians will be imputed for missing values of continuous variables.

Intra-cluster correlation coefficients (ICC) will be calculated using the correlation-based estimation methods for categorical outcomes and analysis of variance methods for continuous variables, respectively.^19^ Generalized estimating equation models with an exchangeable working correlation structure will be conducted to account for the correlations of observations within clusters (hospitals).^20^ Odds ratios for the binary outcomes (DNT ≤ 60 minutes, sICH, favorable functional outcome at 90 days, and death at discharge) and mean differences for the continuous outcomes (DNT, ONT, and mRS score at discharge) will be estimated to assess the treatment effects. Multivariable model for DNT ≤ 60 minutes, DNT, and ONT will be adjusted for patient characteristics (including age, sex, history of stroke/TIA, hypertension, diabetes, atrial fibrillation, coronary heart disease, prior antiplatelet usage, thrombectomy, smoking, prestroke mRS score, and NIHSS score at admission) and hospital characteristics (including hospital grade [tertiary and secondary], stroke unit, teaching hospital status, and annual stroke discharge). Clinical outcomes will be adjusted for age, pre-stroke mRS score, NIHSS score at admission, and other patient characteristics with a p value of <0.1 in the univariate analysis.

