Additionally, to assess whether the improvement in primary and secondary outcomes in the PEITEM group is influenced by the time window, we will conduct a sensitivity analysis with the additional inclusion of patients receiving IVT beyond 4.5 hours upon stroke onset. All patients receiving IVT beyond 4.5 hours upon stroke onset should have CT or MRI core/perfusion mismatch. For patients lost to follow-up at 90 days, we will use multiple imputation as a sensitivity analysis and compared the baseline characteristics between patients with and without mRS at 90 days. A two-tailed P < 0.05 is considered statistically significant. All analyses will be performed using SAS (version 9.4) and R software (version 4.0.5). As no detrimental problems to the participant are anticipated, there are no formal stopping rules for the trial. This trial is registered with ClinicalTrials.gov, number NCT03317639.

**Fig A** Study design and timeframe.

**
[figure not shown]
**

**Fig B** A PEITEM intervention diagram and its relationship with the BCW methods.

[figure not shown]

Abbreviations: BCW, Behaviour Change Wheel; DNT, Door-to-Needle Time.

**Table A** Description of PEITEM Intervention according to the Behavior Change Wheel Components.

| Intervention | Definition | Activity |
| --- | --- | --- |
| **P**ersuasion | Using communication to induce positive or negative feelings or stimulate action | 1. Monthly video teleconference between stroke doctors from PEITEM hospitals and research team for face-to-face problem solving; 2. Monthly DNT feedback by setting up DNT target, time tracking with feedback, discussion about the reasons of delay and improving measures through case discussion. |
| **E**nvironment Reconstruction | Changing the physical or social context | Implementation of standardized medical record templates involving evidence-based performance measures in the electronic medical record. |
| **I**ncentivization | Creating expectation of reward | Establishment of a pioneer award of IVT to the hospitals according to the number of IVT patients and the proportion of DNT ≤60min by research team. |
| **T**raining | Imparting skills | Training of sustainable application of quality improvement tools to help hospitals to establish their own personalized, efficient and stable code stroke workflow via video teleconference. |

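### Covariates for the secondary clinical outcomes are chosen by univariate p<0.1 in the trial data; separately, thrombectomy, given after randomisation, is an adjustment covariate for the DNT and ONT models

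*Protocol*

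**What the plan says.** The Statistical Analysis Plan section of the protocol has two covariate rules.

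- **Process outcomes.** "Multivariable model for DNT ≤ 60 minutes, DNT, and ONT will be adjusted for patient characteristics", followed by a closed list of 12 patient and 4 hospital characteristics. The patient list ends with "prior antiplatelet usage, thrombectomy, smoking, prestroke mRS score, and NIHSS score at admission", so thrombectomy stands beside age, sex and comorbidities.
- **Clinical outcomes.** "Clinical outcomes will be adjusted for age, pre-stroke mRS score, NIHSS score at admission, and other patient characteristics with a p value of <0.1" in a univariate analysis. The part of the set left to the data is thus "other patient characteristics with a p value of <0.1 in the univariate analysis". The pool of other characteristics is not listed for these models, and the univariate test is not named.

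The Outcomes section says: "The DNT is defined as the time between hospital arrival and the initiation of IVT". ONT is defined with the same end point. The same section makes sICH, death and mRS at discharge, and mRS 0-1 at 90 days, secondary outcomes.

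The protocol does not say when thrombectomy is done relative to thrombolysis, whether PEITEM is expected to change its use, or whether the adjusted or the unadjusted GEE estimate is the main one.

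**The concern.** There are two separate defects, and they sit in different models.

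**Selection by p value.** The trial data decide which covariates enter each clinical model. Four outcomes can end with four different models, none known in advance, and the standard error of the final model is computed as if it had been. These outcomes carry the safety and functional message of the trial, so a reader should not have to ask whether their models were settled after the results were seen. The sponsor already names a closed list for the process outcomes, so the looser rule is not a necessity.

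**A post-randomisation covariate.** Hospitals are randomised and thrombectomy happens later, in hospital. PEITEM works on in-hospital care; Table A says its training should "help hospitals to establish their own personalized, efficient and stable code stroke workflow via video teleconference". If the intervention alters who gets thrombectomy, conditioning on it no longer compares the arms as randomised. For DNT and ONT there is a further problem of order: a thrombectomy done after thrombolysis starts cannot explain an interval that has already closed.

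**Working it through.** The protocol gives no figure on this point to reproduce. The checks below are illustrations, with assumptions stated.

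**1. Number of candidates.** The patient list has 12 entries, and 3 (age, pre-stroke mRS, admission NIHSS) are forced into the clinical models: 12 − 3 = 9. That these nine form the pool is an inference.

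**2. How often irrelevant covariates enter.** If all nine are unrelated to the outcome and the tests are independent:
- expected number selected = 9 × 0.1 = 0.9
- chance of at least one = 1 − 0.9^9 = 0.613, or 61% per outcome

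If the test ignores clustering (22 clusters of 65, outcome ICC 0.05, 2,000 simulated trials), one irrelevant covariate is selected in 9.3%, 10.8% and 13.0% of trials for covariate ICC 0, 0.02 and 0.05.

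**3. What selection does to the treatment test.** Simulated false-positive rates at nominal 5%: 22 clusters of 65, no treatment effect, exchangeable GEE, 600 runs per row, simulation error about 1 point, covariate strengths and ICC assumed.

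| Scenario | 3 fixed | 3 fixed + p<0.1 | all 12 |
|---|---|---|---|
| 9 irrelevant candidates, common outcome | 7.5% | 7.7% | 7.0% |
| 4 prognostic candidates | 6.5% | 6.8% | 6.7% |
| rare outcome | 7.7% | 8.7% | 9.3% |

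Selection adds nothing that can be told from simulation error. The excess over 5% is also there without selection, so it has another source.

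**4. Thrombectomy and the primary outcome.** Let Y be DNT ≤60 minutes, A the arm, and let the log-odds of thrombectomy be b + aA + gY. By Bayes' rule, adding thrombectomy to a logistic model for Y multiplies the arm odds ratio by

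R = [(1+e^(b+a)) / (1+e^(b+a+g))] ÷ [(1+e^b) / (1+e^(b+g))].

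If a = 0 (no effect of PEITEM on thrombectomy), R = 1. Now assume b = −2.0 (about 12% thrombectomy) and a two-fold rise in its odds, a = ln 2:
- g = +0.5: R = (1.2707/1.4463) ÷ (1.1353/1.2231) = 0.947
- g = −0.5: R = (1.2707/1.1642) ÷ (1.1353/1.0821) = 1.040

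With a two-fold fall instead, R is 1.035 and 0.978. With 5% thrombectomy, a two-fold rise and g = ±0.2, R is 0.990 and 1.008, a shift of about 1%.

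The design difference is "a change from 55% to 70% of patients with DNT ≤ 60 minutes is clinically important", an odds ratio of (0.70/0.30)/(0.55/0.45) = 1.91. The extremes above would turn it into 1.91 × 0.947 = 1.81 or 1.91 × 1.040 = 1.99.

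**5. Thrombectomy and a clinical outcome.** Simulation of 400,000 patients per row without clustering. Assumed: conditional odds ratio for PEITEM e^0.2 = 1.22; thrombectomy changes the outcome log-odds by ±0.5; unmeasured severity either absent or driving both thrombectomy and outcome.

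| PEITEM → thrombectomy (log-odds) | thrombectomy → outcome | shared severity | OR without | OR with | change |
|---|---|---|---|---|---|
| −0.5 | −0.5 | no | 1.246 | 1.220 | −2.1% |
| −0.5 | −0.5 | yes | 1.195 | 1.146 | −4.1% |
| −0.5 | +0.5 | no | 1.193 | 1.221 | +2.3% |
| −0.5 | +0.5 | yes | 1.170 | 1.164 | −0.5% |
| +0.5 | −0.5 | no | 1.186 | 1.228 | +3.5% |
| +0.5 | −0.5 | yes | 1.161 | 1.244 | +7.1% |
| +0.5 | +0.5 | no | 1.254 | 1.218 | −2.9% |
| +0.5 | +0.5 | yes | 1.225 | 1.232 | +0.6% |

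Four rows fall and four rise. When PEITEM leaves thrombectomy use unchanged, the odds ratio moves by no more than about 0.3% (for example 1.209 to 1.211).

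**The case against.** The strongest reply is that little is at stake. The affected outcomes are secondary, the protocol does not rank adjusted above unadjusted estimates, and the simulation in step 3 shows no detectable inflation from the selection. No PEITEM component targets thrombectomy. All of this stands, and it limits the size of the point. It does not make the rules sound: both are stated rules, not details left to a later document, and both can be put right at no cost.

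A reader might infer more than the protocol supports:

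- *That the primary result is data-driven.* It is not. DNT ≤60 minutes, DNT and ONT have a closed list, and the p<0.1 rule does not touch them.
- *That thrombectomy is in every model.* It is named once, in the list for the process outcomes. For clinical outcomes it is only a possible entrant, because the protocol classes it as a patient characteristic.
- *That adjustment removes part of PEITEM's effect.* This needs PEITEM to change thrombectomy use, which the protocol does not state, and even then the bias may run either way (steps 4 and 5).
- *That 61% is an error rate.* It is the chance that some irrelevant covariate enters a model, not the chance of a wrong conclusion about PEITEM.

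**Conclusion.** The point holds as a modest improvement to the analysis plan. The clinical models are not fixed in advance. Their standard errors ignore the selection, although its effect on false-positive rates was too small to detect under the assumptions of step 3.

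Thrombectomy does not belong in models for intervals that end when thrombolysis starts, unless it is justified as an indication known before treatment, and no such justification is given. The resulting bias is of unknown direction and is zero or negligible if PEITEM leaves thrombectomy use unchanged. It is probably small for the primary outcome: about 1% of the odds ratio under weak associations, and about 5% with a two-fold difference in thrombectomy odds and a stronger association with DNT. For a clinical outcome the illustrations span −4% to +7%. These sizes rest on assumed thrombectomy rates and associations; the protocol gives none.

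**What to change.** In the Statistical Analysis Plan section:

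1. Replace the p<0.1 rule by one named set of baseline covariates used for all clinical outcomes. It should contain at least age, pre-stroke mRS and admission NIHSS, which are already forced in. Any further baseline covariate should be named before outcomes are seen by arm. For sICH and death at discharge, if events are few, there is good reason to keep to those three.
2. Remove thrombectomy from the list for DNT ≤60 minutes, DNT and ONT, and state that it is not a covariate in the clinical models.
3. Report thrombectomy by arm as a description of care, or use it only in a labelled sensitivity analysis.

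The remaining covariates for the primary outcome can stay as they are. The cost is a change of wording. Sample size and conduct are unaffected, and no new data are needed, since the present model already requires thrombectomy to be recorded.

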**Participants: study clusters and their patients**

In China, hospitals are classified into 3 grades: community hospitals are defined as primary grade, hospitals that serve several communities are defined as secondary

grade, and central hospitals for a certain district or city are defined as tertiary grade. Only secondary or tertiary public hospitals with emergency departments (EDs) and neurological wards that admit patients with stroke and had the capacity to administer intravenous rtPA were eligible to participate in this trial. Hospitals participating in the Zhejiang Stroke Alliance meeting the inclusion and exclusion criteria are eligible for inclusion in the MISSION trial. Hospitals meeting the following criteria are eligible for the study: (1) agree to participate in the ongoing data report and continuous audit of IVT processes of care and outcomes; (2) have a stroke unit or staffing equivalent to a stroke physician and a nurse. The hospitals with fewer than 20 thrombolytic cases per year will be excluded. Only the AIS patients receiving IVT within 4.5 hours are eligible for inclusion.

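### The re-run that adds patients treated beyond 4.5 h tests robustness to the eligibility limit; it does not estimate whether the PEITEM effect varies with the time window, which is its stated aim

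*Protocol*

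**What the plan says.** The section on participants sets the main population: "Only the AIS patients receiving IVT within 4.5 hours are eligible for inclusion".

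The Statistical Analysis Plan section then adds one further analysis. Its purpose is "to assess whether the improvement in primary and secondary outcomes in the PEITEM group is influenced by the time window". Its method is "we will conduct a sensitivity analysis with the additional inclusion of patients receiving IVT beyond 4.5 hours upon stroke onset". On who these extra patients are, it says: "All patients receiving IVT beyond 4.5 hours upon stroke onset should have CT or MRI core/perfusion mismatch".

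The same section plans GEE models with an exchangeable correlation by hospital, giving odds ratios and mean differences by arm. It contains no interaction term, no separate estimate for late patients and no rule for comparing the two runs. The expected number of late patients is not stated anywhere.

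Under Outcomes, DNT runs from hospital arrival to the start of IVT and ONT from symptom onset to the start of IVT. Both are on the list of recorded data, and that section says data on all thrombolysed patients will be entered.

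**The concern.** Purpose and method do not match. Asking whether an improvement is influenced by the time window is a question about effect modification: is the arm difference the same for patients treated early and late? The method estimates one average arm difference in early and late patients together. As the enlarged set contains every main-set patient, the two estimates share most of their data and will tend to agree for that reason alone.

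The report could then present two similar estimates as evidence that the benefit does not depend on the window, although neither run estimates the effect in late patients or its uncertainty. The primary analysis is not affected.

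**Working it through.** **The plan's own figures.** The effect size comes from the Sample size section: "a change from 55% to 70% of patients with DNT ≤ 60 minutes is clinically important", a difference of 15 points, odds ratio (0.70/0.30)/(0.55/0.45) = 1.91. The size is "a total of 1424 patients at 22 hospitals will be required", that is 712 per arm and 1424/22 = 64.7 per hospital, with ICC 0.05.

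- Design effect: 1 + (64.7 − 1) × 0.05 = 4.19.
- Two-sided 5% power for 55% against 70% with 712/4.19 effective patients per arm: 81.8%, in line with the stated 80%. The total of 1424 was not matched exactly (1365 without and 1474 with a continuity correction), but nothing below depends on that.

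**How far the enlarged-set estimate can move.** Let s be the late share of the enlarged set. Assumptions: s is equal in both arms, and the control rate is 55% in early and late patients alike. Then

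enlarged-set effect = (1 − s) × main effect + s × late effect.

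The protocol does not give s, so a range is shown, with a main effect of 15 points:

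| s (assumed) | Late effect 0: points (OR) | Late effect −15: points (OR) |
| --- | --- | --- |
| 2% | 14.7 (1.88) | 14.4 (1.86) |
| 5% | 14.25 (1.84) | 13.5 (1.78) |
| 10% | 13.5 (1.78) | 12.0 (1.66) |
| 20% | 12.0 (1.66) | 9.0 (1.46) |
| 30% | 10.5 (1.55) | 6.0 (1.28) |

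Up to a 10% late share, complete loss of effect in late patients moves the estimate by at most 1.5 points. At 20% to 30% the movement is 3.0 to 4.5 points.

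**The right yardstick for that movement.** The main estimate has standard error sqrt((0.55 × 0.45 + 0.70 × 0.30) × 4.19/712) = 5.19 points, so a 95% half-width of 1.96 × 5.19 = 10.2 points. That is not the error of the difference between the two runs, because they are nested. Algebraically,

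enlarged-set − main = s × (late effect − main effect),

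so its standard error is s × SE(late − main). Hospital effects are taken to cancel within hospital. At s = 10% there are 1424 × 0.10/0.90 = 158 late patients, 79 per arm.

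- Late effect 0: SE(late − main) = sqrt((0.2475 + 0.2475)/79 + (0.2475 + 0.21)/712) = 8.3 points. The SE of the shift is 0.83, and the 1.5-point shift is 1.8 SE.
- Late effect −15: SE(late − main) = sqrt((0.2475 + 0.24)/79 + (0.2475 + 0.21)/712) = 8.3 points. The SE of the shift is 0.83, and the 3-point shift is about 3.6 SE.

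The information is thus partly in the data, but the plan does not extract it: it specifies neither the difference between the runs nor its standard error.

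**What a direct contrast could achieve.** Approximate power to detect a late effect of 0 against a main effect of 15, on the same assumptions, is Φ(15/SE − 1.96):

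| s (assumed) | Late patients | Power |
| --- | --- | --- |
| 2% | 29 | 12% |
| 5% | 75 | 25% |
| 10% | 158 | 44% |
| 20% | 356 | 73% |
| 30% | 610 | 88% |

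**ONT as an outcome.** The re-run also covers secondary outcomes. Late patients have long ONT by definition, so unequal late shares move the mean difference by themselves. With assumed mean ONT of 160 min (main) and 400 min (late), shares of 5% and 10% by arm give (0.10 − 0.05) × (400 − 160) = 12 min with no difference in effect between windows.

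**Why the late group is not a clean subgroup.** ONT = onset-to-door time + DNT. PEITEM aims to shorten DNT, so it can bring a borderline patient inside 4.5 h. Which patients count as late therefore depends partly on arm. Onset-to-door time, ONT − DNT, is fixed before arrival.

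**The case against.** The strongest defence is that the analysis is labelled a sensitivity analysis and follows directly from the 4.5 h eligibility limit. Read as asking whether the result depends on that limit, re-running on the wider set is the standard method and needs no interaction. A separate statistical analysis plan, not seen here, might also add detail. The first part stands: the run is valid for that purpose and should be kept. It does not rescue the sentence as written, because the protocol itself states the aim as influence of the time window and ties this method to it.

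Three stronger readings are tempting and are not supported.

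- A reader might infer that the re-run returns almost the same answer whatever the truth. That needs a small late share, which the protocol does not give. At 30% the odds ratio falls from 1.91 to 1.55 with no late effect, and to 1.28 with a reversed one. ONT can shift through unequal late shares alone.
- A reader might set the shift against the 10.2-point half-width of the main effect and call it undetectable. For nested sets that is the wrong comparison. At a 10% late share, a full reversal gives a shift of about 3.6 of its own standard errors.
- A reader might infer that mismatch imaging delays the needle and makes late patients' DNT non-comparable. The protocol says only that late patients "should have CT or MRI core/perfusion mismatch", in both arms alike. It does not say how long this takes or that earlier patients lack such imaging. A higher DNT level in both arms would not by itself bias the comparison of arms.

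It is also fair to object that a direct contrast has low power when late patients are few. That stands, but its confidence interval would show the uncertainty, whereas two similar overall estimates conceal it.

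**Conclusion.** The mismatch between aim and method is real and limited to one secondary check. The planned run answers whether the result is robust to the 4.5 h limit; it does not estimate how the effect varies with the window. With a 15-point main effect and no effect in late patients, the enlarged-set estimate would be 14.3 points at a 5% late share, 13.5 at 10% and 10.5 at 30%. These figures rest on an assumed late share, equal in both arms, and a common 55% control rate.

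The protocol sets no rule that similar estimates prove independence from the window, so the risk is one of interpretation. The change is a cheap improvement.

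**What to change.** 1. Keep the re-run on the enlarged set, described as robustness to the 4.5 h eligibility limit.
2. For the stated aim, add an arm-by-onset-to-door-time interaction (ONT minus DNT) to the planned GEE and report it with its confidence interval. Fit it to the enlarged set. In the main set, any patient arriving more than 210 min after onset must have DNT below 60 min to be treated within 270 min, so no arm difference in the primary outcome is possible there. The mismatch requirement means the enlarged set lessens this truncation but may not remove it.
3. Give the number of patients treated beyond 4.5 h and their estimates by arm, marked as descriptive only, because that group is defined by an interval that contains DNT.
4. If the interaction is not added, reword the aim as robustness to the 4.5 h limit and draw no conclusion about the time window.

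The cost is one model term and one table, from data already recorded, with no change to conduct or to the primary analysis. The drawback is imprecision: the approximate power of a direct late-versus-main contrast is 25% at a 5% late share and 44% at 10%. The interaction on onset-to-door time is a different contrast whose power was not calculated, but it should also be read from its interval. Onset-to-door time is also not identical to the onset-to-needle window in the text, and the plan should say so.
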